## Abstract

**Background::**

The optimal and safest hypnotic agent for rapid sequence intubation in critically ill patients remains uncertain. Factors such as hypovolemia, vasoplegia, hypoxemia, and acidosis can influence the efficacy and safety of induction agents. Propofol is commonly used for this purpose; however, it is associated with the risk of exacerbating hypotension. Ketamine, which has a more favorable hemodynamic profile, may offer a safer alternative in these patients.

**Objective::**

To assess whether ketamine is a safer alternative to propofol for rapid sequence intubation by reducing the incidence of hypotension during induction in critically ill patients.

**Methods::**

This will be a randomized, open-label, pragmatic, bicenter study. A total of 170 critically ill patients requiring endotracheal intubation in the intensive care unit will be randomly assigned to receive either ketamine or propofol as the hypnotic agent. Randomization will be conducted using RedCap with a 1:1 ratio and variable block sizes, stratified by study site and vasopressor use during intubation.

**Results::**

The primary outcome will be the occurrence of hypotension, defined as the lowest mean arterial pressure recorded within the first 10 minutes following induction. Secondary outcomes, assessed within 1-hour post-induction, include mortality, incidence of cardiopulmonary arrest, the occurrence of severe hypotension (systolic blood pressure < 80mmHg), the occurrence of severe hypoxemia (oxygen saturation < 85%), and the number of intubation attempts.

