## INTRODUCTION

Rapid sequence intubation (RSI) is a series of actions aimed at promptly and safely securing a definitive airway via orotracheal intubation in patients at risk of aspiration,^(1)^ However, this procedure may result in hemodynamic disturbances.^(2,3)^

The RSI algorithm typically involves pre-medication, induction with a hypnotic agent, and neuromuscular blockade before laryngoscopy.^(4)^ The primary hypnotic agents utilized for this purpose include propofol and ketamine.^(5)^ Propofol, an alkylphenol derivative, is a highly lipophilic agent with potent hypnotic properties. However, it may negatively affect myocardial contractility and vasodilation, resulting in hypotension.^(4)^ In contrast, ketamine, a phencyclidine derivative, exhibits cardiovascular stimulant effects that may increase blood pressure, heart rate (HR), and cardiac output, leading to an increase in myocardial oxygen demand and a potential rise in intracranial pressure.^(6)^ However, in critically ill patients, physiological alterations induced by stress and disease processes may modulate the hemodynamic response to ketamine, and some studies have also reported hypotension associated with its use.^(7,8)^

Several studies have compared various RSI agents and their effect on hemodynamics,^(4)^ though most of these studies were conducted in operating rooms^(9)^ or emergency departments.^(10,11)^ Despite this, there remains a lack of randomized controlled trials comparing the use of propofol *versus* ketamine in critically ill patients. Prior studies comparing ketamine with etomidate^(12)^ or the combination of propofol and ketamine with etomidate^(4)^ found no significant differences in clinical outcomes.

Given this uncertainty, there is a need for controlled, prospective studies to evaluate its impact on complications associated with intubation. We hypothesize that ketamine is a safe alternative for RSI in intensive care unit (ICU) patients and may be associated with a lower incidence of hypotension and other complications compared to propofol. Therefore, the primary objective of this study is to assess whether ketamine is a safer alternative to propofol for RSI by reducing the incidence of hypotension during induction in critically ill patients.

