If the first attempt is unsuccessful, the patient will be reoxygenated before another attempt is made. If intubation remains unsuccessful after two attempts, a qualified alternate operator or adjunct devices will be utilized. If additional medications are required, the study hypnotic agent will be used, with dosing at the discretion of the attending team. All intubation steps will follow a strict protocol, and patients will undergo an intubation checklist as per routine in the participating units (Figure 2S - Supplementary Material). Continuous monitoring will be performed using electrocardiography, pulse oximetry, and invasive or non-invasive blood pressure monitoring. The monitor will proceed with measurements every 2 minutes for patients with noninvasive blood pressure measurement. The use of vasoactive drugs before induction will be initiated only if the patient's mean arterial pressure (MAP) is below 65mmHg, following the institutional protocol. Doses of vasoactive drugs can be adjusted during the procedure at the discretion of the ICU team. In both groups, general management, such as pre-oxygenation, ventilatory support, and use of adjunctive devices, will follow the ICU protocol (Supplementary Material). Data on adherence to the study protocol, including successful medication administration, will be collected for all patients who undergo intubation in both groups. Any instances patients do not receive the assigned medication will be documented, including the reason for non-administration.

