### Outcomes

The study's primary outcome is the lowest MAP recorded within the first 10 minutes following the induction for intubation.

Secondary outcomes include:

–Average MAP within the first hour after induction.–Mortality within the first hour after induction.–Cardiac arrest within the first hour after induction.–Occurrence of severe hypotension, defined as systolic blood pressure (SBP) < 80mmHg, within 1 hour after induction.–Occurrence of severe hypoxemia, defined as peripheral oxygen saturation (SpO_2_) < 85%, within one hour after induction.–Time for successful intubation.

Tertiary outcomes include:

–The number of intubation attempts.–The highest HR within 1 hour after induction.–The total dose of vasopressors administered within the first 24 hours, using the noradrenaline equivalent dose.–Mean change in vasopressor dose (norepinephrine equivalent) from baseline to hour 1.–Ventilator-free days within the first 7 days, defined as the number of days on which individuals are able to breathe spontaneously without any invasive ventilatory assistance, ascribing zero days to those who die within 7 days.–Mortality at day 7.–ICU mortality.–Hospital mortality.

Safety outcomes will be assessed during the first 10 minutes following induction, and will include:

–Hypertension, defined as SBP > 180mmHg.–Laryngospasm, as reported by the physician in charge of intubation.–Bradycardia, defined as HR < 45 bpm.–Arrhythmias.–Bronchoaspiration, defined as the presence of gastric content aspirated into the airway during intubation.

All outcome data will be presented as specified on the electronic supplemental materials (Table 1S - Supplementary Material). The trial sequence is available in figure 1.

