#### Statistical analysis

Our primary analysis will follow a modified intention-to-treat (mITT) approach. As clinical management might change after randomization, we expect that some patients who will be randomized will not be intubated. Similarly, as we will use a deferred (opt-out) consent process, some patients (or representatives) might not consent. Thus, our mITT analysis will include only those patients who will be intubated and who consent to participate. The data analysis will be performed after submitting the protocol paper and analysis plan for publication.

Categorical variables will be expressed as counts and percentages. Continuous variables will be presented as means and standard deviations (SD) or medians with interquartile ranges (IQR, 25th -75th percentile) as appropriate. For all outcomes, including the primary outcome, we will not impute missing data, and the number of missing values will be clearly presented in tables. Treatment adherence will be reported as each group's mean (SD) number of successful medication administrations.

The primary outcome (lowest MAP within the first 10 minutes post-induction) will be analyzed using a linear regression model, adjusted for baseline MAP before induction, total vasopressor dose in the first 10 minutes, age, and a random patient intercept. A MAP value of 10mmHg (the average cardiovascular filling pressure) will be considered in patients with cardiac arrest.^(14)^ Other vasopressors will be converted to noradrenaline dose equivalents. A per-protocol analysis will be performed, including only patients who received the assigned medication. Additionally, we conducted sensitivity analysis considering the lowest measured blood pressure before cardiac arrest and an unadjusted analysis. In all primary outcome analyses, the effect estimate will be expressed by the mean difference with 95% confidence intervals (95%CI) and p values reported.

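### The objective, hypothesis and abstract are worded as incidence of hypotension, but the trial is defined, sized and analysed for mean lowest MAP, which does not by itself establish a lower incidence

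*Protocol article*

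**What the plan says.** The primary question is worded as an event:

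- The abstract's Objective is to show that ketamine is safer "by reducing the incidence of hypotension during induction in critically ill patients".
- The Introduction repeats this: "the primary objective of this study is to assess whether ketamine is a safer alternative to propofol for RSI by reducing the incidence of hypotension". The hypothesis just before it also expects a lower incidence of hypotension with ketamine.
- The abstract's Results paragraph says: "The primary outcome will be the occurrence of hypotension, defined as the lowest mean arterial pressure recorded within the first 10 minutes following induction".

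The operative sections use a continuous measure:

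- Outcomes: "The study's primary outcome is the lowest MAP recorded within the first 10 minutes following the induction for intubation". No cut-off is given.
- Sample size calculation: a 10 mmHg difference in lowest MAP, SD 20 mmHg, alpha 0.05, 90% power, 170 patients.
- Statistical analysis: the outcome "will be analyzed using a linear regression model, adjusted for baseline MAP before induction" and other terms, reported as a mean difference with 95% CI.
- Discussion: lowest MAP within 10 minutes, again without a threshold.

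The only hypotension event in the outcome lists is a secondary outcome, severe hypotension (SBP below 80 mmHg) within 1 hour. The safety outcomes for the first 10 minutes include hypertension and bradycardia, but not hypotension.

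**The concern.** The abstract's definition cannot classify a patient. Without a threshold, a lowest MAP does not say whether hypotension occurred. The same event wording appears in the objective and the hypothesis, so this is more than one loose phrase.

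What is at stake is the claim that a positive primary result can carry. A higher mean lowest MAP is not the same finding as fewer hypotensive patients. The Introduction itself says that ketamine may raise blood pressure, so part of a mean difference could come from patients who would not have been hypotensive on either drug. The mean also reacts to how low a value is. Cardiac arrest is scored as 10 mmHg, which moves an arm's mean but adds nothing to an event count if that patient was already below the threshold. If the objective stays as worded, its answer would rest on an analysis that estimates something else.

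**Working it through.** **1. What the sample size was calculated for.** Inputs from Sample size calculation: difference 10 mmHg, SD 20 mmHg, alpha 0.05, power 90%. The two-sided test comes from Statistical analysis, and 1:1 allocation from Randomization and concealment.

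n per arm = 2 × (1.960 + 1.282)² × 20² / 10² = 2 × 10.51 × 4 = 84.1, rounded up to 85, so 170 in total. This matches the plan.

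Power at 85 per arm: 10 / (20 × √(2/85)) = 3.26; 3.26 − 1.96 = 1.30, giving 90.3%. The noncentral t calculation gives 90.0%.

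The trial is therefore sized for a difference in means, and size and model agree with each other.

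**2. What a 10 mmHg mean difference implies for incidence.** The protocol gives no arm means and no outcome cut-off, so both are assumptions here: lowest MAP normal in each arm with SD 20, ketamine shifted up by 10 mmHg, cut-off 65 mmHg for illustration only, and propofol mean varied from 55 to 75.

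Event rate = Φ((65 − mean)/20).

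Power = Φ[(|p₁ − p₂| − 1.96 × √(2p̄(1 − p̄)/85)) / √(p₁(1 − p₁)/85 + p₂(1 − p₂)/85)].

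| Mean lowest MAP, propofol / ketamine | Below 65, propofol | Below 65, ketamine | Difference (points) | Power, 85 per arm |
|---|---|---|---|---|
| 55 / 65 | 69.1% | 50.0% | 19.1 | 72% |
| 60 / 70 | 59.9% | 40.1% | 19.8 | 73% |
| 65 / 75 | 50.0% | 30.9% | 19.1 | 72% |
| 70 / 80 | 40.1% | 22.7% | 17.4 | 69% |
| 75 / 85 | 30.9% | 15.9% | 15.0 | 64% |

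Worked row, 60 / 70: p₁ − p₂ = 0.1974; 1.96 × 0.0767 = 0.1503; (0.1974 − 0.1503)/0.0752 = 0.63; Φ(0.63) = 0.73.

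The same mean difference corresponds to 15 to 20 points of incidence, depending on where the arms lie, and power for the event comparison is 64% to 73%.

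**3. The uniform shift is itself an assumption.** Take the third row, where half of the propofol patients lie below 65. In a constructed extreme, the half below gains nothing and the half above gains 20 mmHg. The mean difference is 0.5 × 0 + 0.5 × 20 = 10 mmHg and the difference in incidence is zero. This is not a forecast. It shows only that the mean difference does not determine the incidence difference.

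**4. Whether a listed outcome fills the gap.** The objective concerns hypotension during induction. The severe hypotension outcome runs to 60 minutes, six times the primary window, and is based on SBP. It includes events in the first 10 minutes but does not separate them, and it misses hypotension less extreme than SBP below 80 mmHg. No event outcome is defined for the 10-minute window itself.

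**The case against.** The strongest reply is that this is a matter of wording. Every operative section agrees on lowest MAP within 10 minutes, the sample size reproduces, the model fits the outcome, and even the abstract's sentence names lowest MAP as the definition. A continuous primary outcome with a severe-hypotension secondary is a legitimate design. All of that stands. What it leaves is the mismatch between the stated objective and the quantity estimated.

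Four stronger readings are tempting, and the document does not support them:

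- *No hypotension is counted in the first 10 minutes.* SBP below 80 mmHg within 1 hour includes those minutes, and haemodynamics are recorded every 2 minutes then. What is missing is an event outcome specific to that window. Supplementary Table 1S, which governs how outcomes are presented, is also not at hand, so the point can be made only about the listed outcomes.
- *The trial is underpowered.* The 64% to 73% concerns an endpoint that is not the primary outcome and should not replace it. The 90% is stated for the mean difference and is correct for it.
- *The protocol already defines hypotension as MAP below 65 mmHg.* The words "mean arterial pressure (MAP) is below 65mmHg" appear in Interventions only as the condition for starting vasoactive drugs before induction. Patients near that level beforehand might cross it whichever drug they receive.
- *The investigators will report a reduced incidence.* That is a prediction. The analysis section fixes a mean difference as the report, and the Discussion speaks of haemodynamic stability. The risk comes from the objective's wording, not from a stated intention.

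**Conclusion.** The point holds as a contradiction within the current text. The objective, hypothesis and abstract promise an effect on incidence or occurrence of hypotension; the outcome definition, sample size, analysis and Discussion deliver a mean difference in lowest MAP. The 170 patients and 90% power apply only to a 10 mmHg mean difference, and that difference cannot by itself establish fewer hypotensive patients.

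This does not undermine the primary analysis. It limits what the analysis may be said to show, which is worth settling before the data are analysed. The contradiction and the reproduced sample size rest on the document alone. The incidence figures and the 64% to 73% rest on assumed normality, a uniform shift, an illustrative cut-off and assumed arm means.

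**What to change.** 1. Reword the Objective and Results paragraphs of the abstract, and the hypothesis and primary objective in the Introduction, to mean lowest MAP within 10 minutes after induction. Limit the primary claim to MAP. This costs a few sentences; the 170 patients, the primary model and the power are untouched.

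2. If any claim about incidence is to be kept, add one secondary binary outcome: hypotension within 10 minutes after induction, reported as a risk difference with 95% CI (the plan now gives only odds ratios for binary outcomes). The steering committee should fix the cut-off before analysis and without sight of results by arm. MAP below 65 mmHg is one option, provided the text says that its present use in the protocol is only as a vasoactive-drug trigger. The 2-minute readings already planned supply the data.

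The downside of the second step is one more unpowered secondary outcome in a plan that makes no multiplicity adjustment. It should be labelled as such and read through its interval. If that is not wanted, the first step alone resolves the contradiction.

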**Conclusion::**

The PROMINE study will provide valuable evidence to guide the selection of hypnotic agents for rapid sequence intubation in critically ill patients. It will contribute to a better understanding of the hemodynamic effects associated with propofol and ketamine in this context, potentially informing clinical practice.

## INTRODUCTION

Rapid sequence intubation (RSI) is a series of actions aimed at promptly and safely securing a definitive airway via orotracheal intubation in patients at risk of aspiration,^(1)^ However, this procedure may result in hemodynamic disturbances.^(2,3)^

The RSI algorithm typically involves pre-medication, induction with a hypnotic agent, and neuromuscular blockade before laryngoscopy.^(4)^ The primary hypnotic agents utilized for this purpose include propofol and ketamine.^(5)^ Propofol, an alkylphenol derivative, is a highly lipophilic agent with potent hypnotic properties. However, it may negatively affect myocardial contractility and vasodilation, resulting in hypotension.^(4)^ In contrast, ketamine, a phencyclidine derivative, exhibits cardiovascular stimulant effects that may increase blood pressure, heart rate (HR), and cardiac output, leading to an increase in myocardial oxygen demand and a potential rise in intracranial pressure.^(6)^ However, in critically ill patients, physiological alterations induced by stress and disease processes may modulate the hemodynamic response to ketamine, and some studies have also reported hypotension associated with its use.^(7,8)^

Several studies have compared various RSI agents and their effect on hemodynamics,^(4)^ though most of these studies were conducted in operating rooms^(9)^ or emergency departments.^(10,11)^ Despite this, there remains a lack of randomized controlled trials comparing the use of propofol *versus* ketamine in critically ill patients. Prior studies comparing ketamine with etomidate^(12)^ or the combination of propofol and ketamine with etomidate^(4)^ found no significant differences in clinical outcomes.

Given this uncertainty, there is a need for controlled, prospective studies to evaluate its impact on complications associated with intubation. We hypothesize that ketamine is a safe alternative for RSI in intensive care unit (ICU) patients and may be associated with a lower incidence of hypotension and other complications compared to propofol. Therefore, the primary objective of this study is to assess whether ketamine is a safer alternative to propofol for RSI by reducing the incidence of hypotension during induction in critically ill patients.

## METHODS

### Study design and participating sites

This is an investigator-initiated, randomized, open-label, pragmatic, multicenter study with two parallel groups. Critically ill patients admitted to the ICU who require orotracheal intubation will be randomly assigned to receive either ketamine or propofol as the hypnotic agent during the RSI procedure. The study design adheres to SPIRIT 2025 Statement recommendations.^(13)^

The study will be conducted at two ICUs: the *Hospital São Paulo* ICU at the *Universidade Federal de São Paulo* (UNIFESP), which has 49 beds (coordinating center), and the adult ICU of the *Hospital do Serviço Social da Indústria do Papel, Papelão e Cortiça do Estado de São Paulo* (SEPACO), with 44 beds. Both ICUs serve a mixed population of high-complexity medical and surgical patients. Both institutions have a standardized intubation protocol in place.

### Trial organization and oversight

An independent Data and Safety Monitoring Board (DSMB) will oversee the trial. The Research and Ethics Committee of UNIFESP approved this study under the number 4.846.329, followed by approval from the *Hospital SEPACO* Ethical Committee. Written informed consent will be obtained from all patients or their legally authorized representatives. The study is registered on the clinicaltrials.gov platform (identifier: NCT05092152) and is funded by a research grant from the *Conselho Nacional de Desenvolvimento Científico e Tecnológico* (CNPq).

### Eligibility criteria

Patients with a clinical indication for orotracheal intubation at the participating sites will be eligible for inclusion. Patients will be enrolled upon meeting all inclusion criteria and none of the exclusion criteria, as outlined in table 1. The study sites will maintain continuous records of all patients who meet the inclusion criteria but are not enrolled in the study, along with the reasons for their exclusion, in compliance with the Consolidated Standards of Reporting Trials (CONSORT) guidelines.

**Table 1 t1:** Eligibility criteria

Inclusion criteria	Exclusion criteria
– Age > 18 years – Indication for orotracheal intubation for any reason	– Pregnancy – Know allergy to any of the study drugs (lidocaine, fentanyl, propofol, ketamine, or rocuronium) – History of bradycardia (heart rate < 50 bpm) or atrioventricular block without a pacemaker – Suspected intracranial hypertension – Intubation during cardiac arrest

D - Day; MAP - mean arterial pressure; MV - mechanical ventilation.

### Randomization and concealment

Patients will be randomized to receive either ketamine or propofol via a central, web-based, automated randomization system (RedCap UNIFESP), accessible 24 hours per day. An external individual not involved in the study will generate a list using the randomization tool on random.org. Patients will be randomized in a 1:1 ratio, in blocks of variable size, stratified according to study site and use of vasopressors. The central automated system will maintain the confidentiality of the randomization sequence. Site investigators will be unaware of the block sizes, ensuring adequate concealment of the randomization sequence. The system will allow only one randomization per patient, and study team members at each site will be responsible for enrolling patients and assigning interventions. The flowchart is available in figure 1S (Supplementary Material).

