For secondary binary and exploratory outcomes, logistic regression will be used, with the effect estimate expressed as odds ratios (ORs) and 95%CIs, with their respective p values. Deaths within the specified ranges will be considered zero free days for outcomes related to free days (ventilator-free days in 7 days). Logistic regression models for ordinal data will report proportional ORs. The frequency of adverse events will be expressed as counts and percentages, and comparisons will be made using the Chi-squared test for categorical variables. Secondary outcomes will not be adjusted for covariates.

For the primary outcome, a pre-specified subgroup analysis will evaluate the following groups: patients < 70 *versus* ≥ 70 years old; patients with a Sequential Organ Failure Assessment (SOFA) score < 8 *versus* ≥ 8 points; patients on vasopressor *versus* without vasopressors; and patients with acute respiratory distress syndrome (ARDS) *versus* those without ARDS. Each subgroup analysis will be performed using linear regression, adjusted for baseline MAP before induction, total vasopressor dose in the first 10 minutes, age, and a random patient intercept. Effect estimates will be reported as mean differences with 95%CIs for each subgroup, with respective interaction p values. We will not adjust for multiplicity.

We will consider a significant two-tailed p level ≤ 0.05. Analysis will be performed using R software in the available version (R Foundation for Statistical Computing), Vienna, Austria.

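### Randomization is stratified by site and vasopressor use, but the primary and subgroup models include neither factor, so the reported standard error may be somewhat too large

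*Protocol article*

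**What the plan says.** Under Randomization and concealment, the protocol article states: "Patients will be randomized in a 1:1 ratio", "in blocks of variable size, stratified according to study site and use of vasopressors". There are two sites: "The study will be conducted at two ICUs". The Methods paragraph of the Abstract words the second factor differently: "stratified by study site and vasopressor use during intubation".

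Under Statistical analysis, the primary outcome is analysed by linear regression, "adjusted for baseline MAP before induction, total vasopressor dose in the first 10 minutes, age, and a random patient intercept". The subgroup models repeat this list. Vasopressor status otherwise appears only as a subgroup factor, "patients on vasopressor *versus* without vasopressors". The sensitivity work is a "sensitivity analysis considering the lowest measured blood pressure before cardiac arrest and an unadjusted analysis", and for the remaining endpoints, "Secondary outcomes will not be adjusted for covariates". Study site is therefore in no described model.

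**The concern.** Permuted blocks within strata nearly balance the arms on site and vasopressor use. Differences between strata then contribute almost nothing to the chance variation of the treatment contrast. A model without the strata leaves those differences in its residual variance and reports a standard error that does not reflect the balance achieved. Confidence intervals come out too wide, and the test rejects less often than its nominal 5%.

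Two terms in the stated model might seem to stand in for the strata, but do not:

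- **Random patient intercept.** It is indexed by patient, not site. With one lowest-MAP value per patient it cannot be separated from the residual.
- **Vasopressor dose in the first 10 minutes.** It accumulates after induction, and the Interventions section lets the ICU team adjust vasoactive doses during the procedure. It can respond to the assigned drug and is not the status recorded before allocation.

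At stake is some reported precision and the calibration of the primary test.

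**Working it through.** **Inputs from the protocol article:** two sites, 1:1 allocation, 170 analysed patients, difference 10 mmHg, SD 20 mmHg, 90% power, two-sided 0.05.

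**Assumed, because the documents give no figure:** the share R² of outcome variance explained by the strata, the difference in lowest MAP between vasopressor strata, the site difference, and block sizes of 4 and 6.

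**1. The plan's own figure.** n per arm = 2(1.960 + 1.282)² × 20²/10² = 84.1, rounded up to 85, so 170 in total. Power at 85 per arm is 0.903 (normal) or 0.900 (noncentral t). The stated sample size reproduces, with no contribution from the strata.

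**2. Mechanism, with no other covariates.** Strata omitted, the model reports SE = 20√(2/85) = 3.07 mmHg. Strata included, SE = 20√(1−R²)√(2/85). Under stratified blocks the second value is close to the true SE in both cases. For the analysis that omits the strata, type I error = 2[1 − Φ(1.96/√(1−R²))], and power = Φ[(10 − 1.96 × 3.07)/SE with strata].

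| R² | SE, strata included | Type I error, omitted | Power, omitted | Power, included |
|---|---|---|---|---|
| 0.05 | 2.99 | 0.044 | 0.909 | 0.917 |
| 0.10 | 2.91 | 0.039 | 0.915 | 0.930 |
| 0.20 | 2.74 | 0.028 | 0.927 | 0.954 |
| 0.30 | 2.57 | 0.019 | 0.940 | 0.974 |

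**3. With a prognostic baseline covariate, but no dose term.** Simulation of 3,000 trials of 170 patients; the covariate correlates 0.5 with outcome and is independent of the strata. Monte Carlo error of a 5% rate is √(0.05 × 0.95/3000) = 0.4 percentage points.

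| R² | Omitted: model SE / empirical SE | Type I error | Included: model SE / empirical SE | Type I error |
|---|---|---|---|---|
| 0.05 | 2.66 / 2.56 | 0.043 | 2.57 / 2.56 | 0.051 |
| 0.10 | 2.66 / 2.42 | 0.031 | 2.47 / 2.42 | 0.045 |
| 0.20 | 2.66 / 2.34 | 0.027 | 2.28 / 2.33 | 0.056 |

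**4. With the protocol's own covariates (baseline MAP, age, dose).** Assumed: site difference 5 mmHg, residual SD 16, baseline MAP SD 14 with slope 0.6 and 8 mmHg lower on vasopressors, dose higher on vasopressors.

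| Vasopressor-stratum difference (mmHg) | SE, protocol model | SE, strata added and dose removed | Ratio | Type I error, protocol model | Power at 10 mmHg, protocol model / strata version |
|---|---|---|---|---|---|
| 5 | 2.50 | 2.47 | 1.01 | 4.9% | 97.8% / 97.8% |
| 10 | 2.52 | 2.46 | 1.02 | 4.6% | 97.6% / 98.1% |
| 15 | 2.56 | 2.46 | 1.04 | 4.6% | 97.9% / 98.4% |

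With baseline MAP and age but neither dose nor strata, type I error was 4.6%, 4.4% and 4.1%.

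**5. Spread over wider assumptions.** For the protocol's covariates, type I error was about 4.2 to 5.1% when baseline MAP carries part of the stratum effect and 3.7 to 4.8% when it does not, with the SE up to about 11% too large. A further setting (residual SD 18, site difference 5 mmHg, stratum differences 10, 15 and 20 mmHg) gave 4.6%, 4.5% and 3.1% with a dose term, and 4.7%, 3.4% and 2.5% without it. The 3.1% at 20 mmHg is the one result with the dose term below the 3.7 to 5% range.

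**The case against.** The strongest case against is about size:

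- **Baseline MAP may already carry much of the vasopressor stratum.** The Interventions section ties the start of pre-induction vasoactive drugs to low MAP, and baseline MAP is in the model. This stands, and it is why the effect under the protocol's covariates is small.
- **Large stratum differences are not documented.** A difference of 20 mmHg is twice the 10 mmHg that the steering committee regards as minimally important. This also stands; the result depends on an unknown quantity.
- **The error is conservative and the trial was sized without the strata.** Planned 90% power holds either way.

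The documents do not support four stronger readings that a reader might infer:

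- *That type I error falls to about 3% or lower as a matter of course.* With residual SD 18 and stratum differences of 10 to 20 mmHg, a model with no baseline covariates gives 2.7 to 3.7%. That is not the protocol's primary model.
- *That the benefit of stratifying is lost.* The balance still reduces the true variance; only the reported standard error misses it.
- *That the estimate is biased or false positives are inflated.* Neither follows.
- *That stratum or subgroup is defined by a post-randomization variable.* The abstract's phrase about use during intubation could suggest this. But a stratification factor must be entered before allocation, induction follows randomization at once, and no section builds a model or subgroup on a later version. It is a wording inconsistency.

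That the article leaves covariates to a fuller plan is no defence, because it states the list explicitly.

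**Conclusion.** The mismatch between design and analysis is real; its consequence is minor. With the protocol's covariates and assumed stratum differences of 5 to 20 mmHg, the reported SE is roughly 1 to 11% larger than with the strata included. Type I error is about 3.7 to 5%, apart from the one less favourable result noted. If the strata explain only about 5% of outcome variance, the effect is negligible in practice.

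Whether the post-induction dose belongs in the model is a separate question, but it interacts with this one. Dropping the dose without adding the strata removes the term that partly absorbs the vasopressor effect, and type I error is then about 2 to 4.7%.

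These figures rest on assumed prognostic strength, assumed block sizes, and all 170 analysed patients coming from intact blocks. The foreseen exclusions after randomization could loosen the balance and narrow the gap.

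**What to change.** 1. Add study site and vasopressor use (yes/no, as entered at randomization) as fixed effects in the primary model and in each subgroup model.
2. Define the vasopressor subgroup by that same randomization variable. In that subgroup's interaction model, the stratum term is simply the subgroup main effect.
3. Align the abstract's description of the stratification factor with the Randomization and concealment section, and state in both that it is status at randomization.

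The cost is two degrees of freedom out of 170 patients. Both variables are needed to allocate patients, so they should already be in the randomization system. The sample size does not change. The article places the analysis after submission of the protocol paper and analysis plan, so the change should be fixed in the plan before the data are analysed.
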